### Internal validity

After these procedures, the final version of the KATITA questionnaire will be obtained and the next step will be validity assessment. Briefly, the complete evaluation of a clinical questionnaire requires proof of reliability, validity, sensitivity, and generalizability. Reliability is assessed by internal consistency reliability and test-retest reliability. Validity is evaluated for two main types, construct validity and criterion validity. Construct validity has two components, content validity and convergent validity, and criterion validity also has two components, concurrent validity and discriminant validity.

Cronbach’s alpha is an indicator of internal consistency reliability of a scale, a measure of the correlation of the items in a questionnaire: if all items are measuring the same construct, it will have the value 1; if all are measuring different constructs, it will be zero. Test-retest reliability is established by showing that a patient’s response to a questionnaire item has a high degree of agreement between two applications of the questionnaire separated by a time lag of sufficient length to minimize recall.

Convergent validity, the second component of construct validity, is shown by a high correlation between the questionnaire scores and other measures predicted by theory. Ideally, convergent validity should be demonstrated by high correlations between the scale and validated scales measuring the same or closely related constructs. However, at the present time this will not be possible due to the inexistence of scales measuring tendency to medication non-adherence before the initiation of therapy. Therefore, in this case convergent validity will be assessed with differentiation by known groups, an accepted method of convergent validity analysis where the distributions of scale scores are compared between levels of known predictors of medication non-adherence. If results are within acceptable values, the scale development will proceed to the external validation phase.

### External validity

A prospective, open cohort study involving six kidney transplant centers in three state capitals will include consecutive patients over 18 years-old, of both sexes, who had just been scheduled for kidney transplantation from either a deceased or living donor. Patients will be excluded if they are hospitalized, planned for retransplant, recipients of additional non-kidney transplant, illiterate or with impaired cognition. As shown in Fig 3, the patients will be followed-up for 12 months after kidney transplant.

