#### Pilot questionnaire administration

Thirteen healthcare centers in three capitals of northeastern Brazil states, of which seven are hemodialysis centers and six are tertiary care hospitals performing kidney transplant, will be included and will enroll consecutive patients over 18 years of age, of both sexes, who are in waiting lists for kidney transplant and are able to read and communicate, excluding patients who are candidates for kidney retransplant. The patients will be asked to self-rate each item in a 5-point Likert scale, according to their level of agreement with the presented statement, from 0 (strongly disagree) to 4 (strongly agree). Demographic data will be collected (age, sex, ethnicity, level of education, social support), as well as clinical data related to kidney disease (current dialysis, time on dialysis, etiology of kidney disease and number of blood transfusions). A subsample of the patients will be asked to repeat the administration of the questionnaire after six weeks for assessment of the scale temporal stability through test-retest analysis. These will be consecutive patients who had responded to the questionnaire.

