**Fig 3 pone.0305953.g003:**
[figure not shown]
Diagram of the study design of the external validation study.

At the pre-transplantation, baseline evaluation, demographic and clinical data will be collected, and the KATITA questionnaire will be administered. The questionnaire data will be used for the assessment of predictive validity and of structural validity, which will evaluate whether the factor structure of the KATITA questionnaire is reproduced in this different population. The timing of kidney transplantation after the baseline visit will be variable but expected to be within a short time lag. The next study visit will be at 3 months post-transplant and its purpose will be to assess the concurrent validity of the questionnaire. Concurrent validity is demonstrated by shown a high correlation of the scores of the test scale with those of a validated scale measuring the same or a closely related construct. However, there is no available scale measuring predisposition to medication non-adherence in kidney transplant patients in the pre-transplant setting. To overcome this difficulty and to still obtain a measure of concurrent validity, in addition to the re-administration of the KATITA questionnaire the following two scales were selected to be compared with KATITA at three months post-transplant. The Basel Assessment of Adherence to Immunosuppressive Medication Scale (BAASIS), a widely used questionnaire for assessing adherence to immunosuppressive drugs in adult and adolescent post-transplant recipients, consists of four questions inquiring the patient about the past occurrence of medication non-adherence episodes, two being about the frequency of missed medications doses, one on non-compliance with medication timing, and one asking about having reduced medication doses. Each question has six possible responses, from never (0 points) to everyday (5 points), and thus the questionnaire scores range from 0 to 20, with a score greater than zero classifying the patient as medication non-adherent. The CEAT-VIH scale [29] will also be applied and used as another reference against which the KATITA scores will be compared. This scale was developed to assess medication adherence of persons living with HIV infection and, in addition to questions about non-adherence episodes, includes questions assessing patients’ behavior and beliefs towards their medication. It is a 20-item scale forming a score between 18 and 92, lower scores indicating lower adherence to medication. This scale was selected because it produces an ordinal score measuring the degree of medication non-adherence, which is a distinctive feature from virtually all other medication adherence instruments that only discriminate between adherents and non-adherents, but also because HIV therapy has the same requirements as immunosuppressive therapy in transplant patients regarding strict adherence to the prescribed frequency, dosage, and timing of medication administration. The month 3 study visit will also offer the opportunity of testing KATITA’s sensitivity to change, the ability to respond to a change in state regardless of its clinical relevance to the patient or the clinician, by evaluating whether there was variation in the scale scores after patient exposure to immunosuppressant medication since the pre-transplant evaluation.

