### Sample sizes

For the focus group, eight patients will be selected, which is within the recommended size for focus groups [37]. For the cognitive interviews, sample size will be determined by saturation, that is, when no new information is obtained from participants, but it expected to require no more than 10 patients. For the development of questionnaires measuring a latent construct using factor analysis, and for reliability assessment, there are neither theoretical foundations, nor formal methods of estimation of the required sample size, and the required numbers are based on rules of thumb suggested by several authors, with some recommending a sample size defined by a ratio of participants for each scale item, often 10:1 [38], while others propose a fixed number of participants, independent of the number of items, most commonly in the range of 200 to 300 subjects [39–42]. Accordingly, the sample size for this part of the study will be no less than 300 patients. For the test-retest reliability analysis, a sample size of 20 subjects would be sufficient to ensure 80% power with an alpha error of 0.05 to identify a correlation greater than 0.60, however such small sample will not provide adequate robustness to the results, so a minimum sample size of 60 patients was defined.

The sample size for the external validity study is determined by the requirements for the evaluation of the predictive validity of the KATITA questionnaire. Assuming that the area under the ROC curve (AUROC) of the questionnaire in the prediction of immunosuppressive medication non-adherence would be at least 0.75, and that the proportion of non-adherent patients in the first 12 months after transplant will be about 50%, a sample of 364 patients would estimate the AUROC with an error of ±0.10 with 95% confidence [43]. The same sample size will be used in confirmatory factor analysis for assessment of structural validity of the factorial model, scale sensitivity to change, and concurrent validity assessment.

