### Internal validity assessment

The internal consistency reliability of the final version of the KATITA questionnaire will be evaluated with Cronbach’s alpha for the full scale and for each dimension if a multidimensional scale is obtained, with 95% confidence intervals estimated by bootstrapping. It is generally accepted that for a scale to have clinical application its Cronbach’s alpha must be above 0.80. This statistic will also be used to refine the questionnaire: leaving-one-out Cronbach’s alpha, a Cronbach’s alpha computed excluding one item in turn, should be somewhat smaller than the scale’s Cronbach alpha, otherwise it means that the left-out item is not contributing to the internal consistency reliability. Should factor analysis point to a multidimensional scale, Cronbach’s alphas will be computed for each subscale as well. The same final version of KATITA will be assessed for test-retest reliability using the two-way mixed-effects model, absolute agreement, intraclass correlation coefficient. The generally accepted cutoffs for the coefficient will be adopted: less than 0.50 (poor reliability), 0.50–0.75 (moderate reliability), 0.75–0.90 (good reliability) and greater than 0.90 (excellent reliability). For the evaluation of convergent validity with differentiation by known groups, the Wilcoxon-Mann-Whitney ranksum test will be used to compare KATITA scores between levels of risk factors for non-adherence to immunotherapy medication.

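### The external cohort neither excludes nor identifies patients who answered the pilot questionnaire, so the independence of the confirmatory factor analysis is not secured; Brazilian alpha is also planned only in the item-selection sample

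*Protocol article*

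**What the plan says.** **Development sample** (Pilot questionnaire administration). The centres are "Thirteen healthcare centers in three capitals of northeastern Brazil states, of which seven are hemodialysis centers and six are tertiary care hospitals performing kidney transplant". They enrol consecutive adults "who are in waiting lists for kidney transplant and are able to read and communicate, excluding patients who are candidates for kidney retransplant". Under Sample sizes, "the sample size for this part of the study will be no less than 300 patients".

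**External cohort** (External validity). This is a prospective cohort "involving six kidney transplant centers in three state capitals will include consecutive patients over 18 years-old, of both sexes, who had just been scheduled" for a kidney from a deceased or living donor. The listed exclusions are hospital inpatients, planned retransplant, an additional non-kidney organ, illiteracy and impaired cognition. Earlier participation in KATITA is not on the list. The planned size is 364. The baseline questionnaire data are to "evaluate whether the factor structure of the KATITA questionnaire is reproduced in this different population".

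**Order of the phases** (end of the Introduction). The four phases are sequential.

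**Overlap elsewhere** (Item pool development). Cognitive-interview patients must not have taken part in the focus group.

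**Internal consistency** (Internal validity assessment). Cronbach's alpha is estimated for the final version with bootstrap intervals, and 0.80 is named as the level needed for clinical use. The section adds of alpha: "This statistic will also be used to refine the questionnaire". The External validity assessment section lists no alpha for the Brazilian cohort. The Cross-cultural validation section does list one for Spain.

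**The concern.** A confirmatory factor analysis tests a structure only to the extent that its data did not help to create that structure. Waiting-list patients are the people who are later scheduled for transplant. Both samples are recruited consecutively at transplant hospitals, six in each phase and in three state capitals each time. Under the rule as written, a pilot respondent who reaches scheduling would be enrolled again. That patient would bring similar answers to many of the same items and would be meeting the questionnaire for a second time. Both effects lean towards reproducing the structure.

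The second issue does not depend on overlap. If alpha helps to decide which items stay, alpha in that same sample is somewhat too high for the items that were kept. For the Brazilian version this is the only alpha planned, and it is the one set against 0.80. Under Internal validity, acceptable results at this stage are also the condition for moving to the external phase.

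**Working it through.** **1. Can the samples overlap?**

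| | Development | External validation |
|---|---|---|
| Transplant centres | six, plus seven haemodialysis centres | six |
| Cities | three state capitals, northeastern Brazil | three state capitals |
| Patients | adults on the waiting list | adults just scheduled for transplant |
| Retransplant | excluded | excluded |
| Literacy | able to read | illiterate excluded |
| Bar on earlier participation | not applicable | none listed |

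With sequential phases, nothing in the listed criteria prevents re-enrolment. The Cross-cultural validity section also says that it uses the external study's criteria and then describes them as waiting-list patients, which brings the two populations closer still.

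**2. How large could the overlap be?** The article gives no figure, so the shares below are assumptions.
- 10%: 0.10 × 364 ≈ 36 patients.
- 20%: 0.20 × 364 ≈ 73.
- 30%: 0.30 × 364 ≈ 109.
- Arithmetic ceiling with exactly 300 pilot patients: 300/364 = 82%, leaving 64 new patients.

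**3. How strongly would overlap tie the two samples together?** With m shared patients, N1 = 300, N2 = 364 and an assumed correlation r between a patient's first and repeat answers, the correlation between the two samples' item covariances is roughly m/√(N1·N2) × r². Here √(300 × 364) = 330.5. For m = 36 and r = 0.75 this is 36/330.5 × 0.5625 = 0.06.

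| Shared patients | r = 0.75 | r = 0.90 |
|---|---|---|
| 36 (10%) | 0.06 | 0.09 |
| 73 (20%) | 0.12 | 0.18 |
| 182 (50%) | 0.31 | 0.45 |
| 300 (82%) | 0.51 | 0.74 |

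**4. What does overlap do to a statistic?** An illustrative simulation used 30 items on three factors, loadings from 0.2 to 0.6, 300 development patients, items kept if the item-rest correlation exceeded 0.30, a repeat-answer correlation of 0.8, and 1,500 runs. Mean subscale alpha was:
- development sample: 0.650
- 364 entirely new patients: 0.632
- 10% or 20% overlap: 0.634 for each
- 50% overlap: 0.639
- 82% overlap: 0.642

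Overlap moves the validation value towards the development value, but by only about 0.002 at 10% to 20%. The effect on RMSEA, CFI or chi-square/df was not calculated.

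**5. How optimistic is alpha in the item-selection sample?** The run above gives 0.650 − 0.632 = 0.018. A second simulation used one factor, loadings uniform from 0.1 to 0.6, n = 300, stepwise removal of items with item-rest correlation below 0.30, a fresh sample of 5,000, and 200 runs:
- starting from 20 items: 0.708 against 0.686, a gap of 0.022
- starting from 40 items: 0.841 against 0.833, a gap of 0.008

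The level of alpha depends on the assumed loadings, so only the gap is informative. It is about 0.01 to 0.02. Both simulations apply the item-rest rule alone, not the article's full set of selection rules.

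**The case against.** The strongest reply is that the cohorts do differ by design. One takes anyone on a waiting list, and more than half of its sites are haemodialysis centres. The other takes patients on the point of surgery, includes living-donor recipients, and excludes inpatients and recipients of a further organ. The confirmatory analysis uses newly collected answers from a separately recruited cohort. The six centres are not named, so their identity with the development hospitals is an inference from matching counts. A journal article may also leave the screening of prior participants to the full protocol.

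Much of this stands. A reader might infer that the confirmatory analysis is not independent, or that its fit will be inflated. The article supports neither statement: the overlap could be close to zero, and no effect on fit has been shown. The 82% ceiling would need every pilot patient to be scheduled at one of the six centres during accrual. A reader might also extend the point to predictive validity. That does not follow, because non-adherence at 6 and 12 months plays no part in choosing items, so re-enrolled patients do not create the usual development-sample optimism in the AUROC.

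The point about condensation carries less weight. The article does set out its exclusions, and it bars overlap between the focus group and the cognitive interviews. Above all, it makes a positive claim about the population that its listed criteria do not secure.

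On alpha, it is fair to say that the optimism is small, that bootstrap intervals are planned, and that alpha is computed again in Spain. But the Spanish value belongs to a translated instrument, and a bootstrap of the final item set in the development sample does not remove selection optimism.

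**Conclusion.** The point holds in a limited form. As written, the external cohort can include pilot respondents without their being identified, so the independence of the confirmatory analysis from the sample that generated the structure is not secured. The size is unknown. At an assumed 10% to 20% overlap it is small, with covariance correlations of about 0.06 to 0.18 for repeat-answer correlations of 0.75 to 0.90. It would be material only if a large share were re-enrolled.

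The alpha point stands by itself, even with no overlap. Optimism of about 0.01 to 0.02 in illustrative simulation would change a conclusion only for a scale close to 0.80.

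Neither part undermines the study. The case for acting is that the confirmatory analysis is the only planned structural check of the Brazilian version, and that both remedies are nearly free. If the centres are the same, some would prefer to call the phase temporal validation. The conclusion does not depend on that label.

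**What to change.** 1. At enrolment in the external cohort, record as one yes/no field whether the patient took part in a focus group, a cognitive interview or the pilot questionnaire. Report the number, and repeat the confirmatory factor analysis without those patients. Alternatively, add prior participation to the exclusions.
2. Compute Cronbach's alpha, for the full scale and any subscales, on the external cohort's baseline data. Report it beside the development value as the estimate free of item-selection optimism, leaving out prior participants if there are any.
3. State whether the six centres are the six transplant hospitals of the development phase.

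No repeat of the AUROC is needed on this account.

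The cost is one data field, one repeated analysis and one extra statistic from data already collected. Exclusion instead of flagging would slow accrual slightly and make the sample less strictly consecutive, so flagging is the lighter option. Participation is easy to record at enrolment and may be hard to reconstruct afterwards.

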**Fig 3 pone.0305953.g003:**
[figure not shown]
Diagram of the study design of the external validation study.

At the pre-transplantation, baseline evaluation, demographic and clinical data will be collected, and the KATITA questionnaire will be administered. The questionnaire data will be used for the assessment of predictive validity and of structural validity, which will evaluate whether the factor structure of the KATITA questionnaire is reproduced in this different population. The timing of kidney transplantation after the baseline visit will be variable but expected to be within a short time lag. The next study visit will be at 3 months post-transplant and its purpose will be to assess the concurrent validity of the questionnaire. Concurrent validity is demonstrated by shown a high correlation of the scores of the test scale with those of a validated scale measuring the same or a closely related construct. However, there is no available scale measuring predisposition to medication non-adherence in kidney transplant patients in the pre-transplant setting. To overcome this difficulty and to still obtain a measure of concurrent validity, in addition to the re-administration of the KATITA questionnaire the following two scales were selected to be compared with KATITA at three months post-transplant. The Basel Assessment of Adherence to Immunosuppressive Medication Scale (BAASIS), a widely used questionnaire for assessing adherence to immunosuppressive drugs in adult and adolescent post-transplant recipients, consists of four questions inquiring the patient about the past occurrence of medication non-adherence episodes, two being about the frequency of missed medications doses, one on non-compliance with medication timing, and one asking about having reduced medication doses. Each question has six possible responses, from never (0 points) to everyday (5 points), and thus the questionnaire scores range from 0 to 20, with a score greater than zero classifying the patient as medication non-adherent. The CEAT-VIH scale [29] will also be applied and used as another reference against which the KATITA scores will be compared. This scale was developed to assess medication adherence of persons living with HIV infection and, in addition to questions about non-adherence episodes, includes questions assessing patients’ behavior and beliefs towards their medication. It is a 20-item scale forming a score between 18 and 92, lower scores indicating lower adherence to medication. This scale was selected because it produces an ordinal score measuring the degree of medication non-adherence, which is a distinctive feature from virtually all other medication adherence instruments that only discriminate between adherents and non-adherents, but also because HIV therapy has the same requirements as immunosuppressive therapy in transplant patients regarding strict adherence to the prescribed frequency, dosage, and timing of medication administration. The month 3 study visit will also offer the opportunity of testing KATITA’s sensitivity to change, the ability to respond to a change in state regardless of its clinical relevance to the patient or the clinician, by evaluating whether there was variation in the scale scores after patient exposure to immunosuppressant medication since the pre-transplant evaluation.

The following study visits, at months 6 and 12 post-transplant, will be for evaluation of predictive validity. Predictive validity, the second component of criterion validity, is the ability of a questionnaire score to predict a future outcome, as expected by theory, which represents the criterion or gold standard. The main difference to concurrent validity is that in predictive validity the criterion is measured at a later time than the scale scores, while in concurrent validity both are measured at the same time. In this case, the criterion is obviously medication non-adherence. However, there is no single method for measurement of medication non-adherence that can be considered a gold standard. Methods for measurement of medication non-adherence may be divided into objective methods, including pill count, pharmacy refill records, serum level of immunosuppressants, and electronic monitoring of opening of pill bottles, and subjective methods, such as medication adherence scales, patient self-reporting, and physician impressions. A combination of methods is usually adopted in the evaluation of medication non-adherence to immunosuppressants and, in keeping with this approach, we will use three methods that independently discriminate medication adherent from non-adherent patients: patient self-report of non-adherence using the Morisky Green Levine Medication Assessment Questionnaire (MGL MAQ) [30], the trough serum levels (C_0_ levels) of immunosuppressants measured at the study visits, and reports on pharmacy refill of immunosuppressants. The MGL MAQ tool consists of four questions with a yes/no answer, two being about forgetfulness on taking medication, and two on behavior on taking medication. Patients will also be classified as medication non-adherents if trough serum levels of immunosuppressants measured at each 6- and 12-months study visit are lower than 4 ng/mL for tacrolimus [31], 4 ng/mL for sirolimus [32], 3 ng/mL for everolimus [33], and 50 ng/mL for ciclosporin [34]. All participating healthcare centers belong to the National Health System, which delivers immunosuppressant medication without costs to patients at a central pharmacy, making pharmacy refill records easily accessible for identification of patients who fail to get their medication and who will be considered, in this study, as medication non-adherents. A patient will be considered as non-adherent if being classified as non-adherent by any of the three methods at either the 6-month or the 12-month visit.

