### Statistical analysis

STATA 18 statistical program (Stata Corp., College Station, TX, USA) will be used for statistical analysis. All tests will be two-tailed and results will be considered statistically significant when p<0.05.

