#### External validity assessment

For the analysis of the scale sensitivity to change, the time interval between baseline and transplantation will be presented by the median and interquartile range, and the change will be tested with the Wilcoxon signed rank test comparing baseline to 3-month scores. The magnitude of the change will be interpreted using the standardized response mean (SRM), which is the mean difference between baseline and 3-month post-transplant scores divided by its standard deviation [48], as moderate if SRM>0.5, or large if SRM>0.8. For the evaluation of concurrent validity, Spearman’s rho will be used to estimate the correlation between KATITA scores and the scores of the BAASIS and the CEAP-VIH scales, and the Wilcoxon-Mann-Whitney ranksum test will be used to test the difference in KATITA scores between adherent and non-adherent according to BAASIS. For the evaluation of the predictive validity of the KATITA questionnaire, the AUROC, sensitivity, specificity, positive predictive value and negative predictive value, and corresponding 95% confidence intervals, will be computed for pre-transplant KATITA scores. Structural equation modeling will be used for confirmatory factor analysis, with goodness of fit evaluated with the chi-square test/degrees of freedom statistic, Root Mean Square Error of Approximation (RMSEA), Comparative Fit Index (CFI), Tucker-Lewis index, standardized root mean squared residual and coefficient of determination.

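### Sensitivity to change rests on an uncontrolled before-after test that turns significant at an SRM of about 0.11, so p<0.05 alone cannot separate response from re-administration drift

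*Protocol article*

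**What the plan says.** The External validity section defines sensitivity to change as "the ability to respond to a change in state regardless of its clinical relevance to the patient or the clinician". It proposes to test it at the month 3 visit "by evaluating whether there was variation in the scale scores after patient exposure to immunosuppressant medication since the pre-transplant evaluation".

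The External validity assessment section gives the analysis: "the change will be tested with the Wilcoxon signed rank test comparing baseline to 3-month scores". The SRM is the mean baseline-to-month-3 difference divided by the SD of that difference, interpreted "as moderate if SRM>0.5, or large if SRM>0.8". The Statistical analysis section adds that "All tests will be two-tailed and results will be considered statistically significant when p<0.05". No expected direction is given, and no comparison group or external anchor is named for this analysis. BAASIS and CEAT-VIH are given at month 3 for concurrent validity, not at baseline.

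There is no sample size calculation for this analysis. The Sample sizes section carries over the 364 patients of the predictive validity study: "The same sample size will be used in confirmatory factor analysis for assessment of structural validity of the factorial model, scale sensitivity to change".

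Separately, under Pilot questionnaire administration, "A subsample of the patients will be asked to repeat the administration of the questionnaire". These are at least 60 waiting-list patients (Sample sizes). The only analysis planned for them is the absolute-agreement intraclass correlation of the final scale (Internal validity assessment).

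**The concern.** Between the two administrations the patient is transplanted, starts immunosuppressants, comes off dialysis if previously dialysed, and answers the questionnaire a second time. All of these coincide, so a single-group comparison cannot tell them apart. The SRM does not help with this: its denominator is the SD of change in the same transplanted patients, so it carries no information on movement without transplantation.

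What is at stake is one statement in the results paper. With this sample size a small shift between first and second administration would give p<0.05, and the plan contains nothing against which to judge it. The protocol lists sensitivity among the properties that need proof (Internal validity) and foresees KATITA being used to evaluate interventions on beliefs and behaviours (Introduction). That use depends on knowing whether a moving score reflects a changed state.

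**Working it through.** **The inherited sample size.** The 364 comes from the precision of an AUROC that "would be at least 0.75", with 50% non-adherent and a stated error of ±0.10. With the Hanley-McNeil variance and equal groups, 364 patients give a 95% half-width of 0.04996. It therefore reproduces at ±0.05, a total width of 0.10; ±0.10 would need 92 patients (about 104 with the Obuchowski variance). That is a separate matter. For the present point only the number of pairs counts, and 364 is what the plan assigns.

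**Size of shift that gives p<0.05.** Inputs: n = 364, two-sided alpha 0.05, asymptotic efficiency of the signed rank test 0.955 (roughly normal differences assumed).

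- Just significant: SRM = 1.96/√(364 × 0.955) = 1.96/18.64 = 0.105.
- 80% power: SRM = (1.96 + 0.842)/18.64 = 0.150.
- Power at a true SRM of 0.20: 96%.
- With 20% of patients lost (assumed; 291 pairs): 0.118, 0.168 and 92%.

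The significance threshold is 0.105/0.5 = 0.21, about one fifth of the protocol's moderate mark.

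**Would the test-retest ICC reveal drift of that size?** Let s be the SD of change and δ the mean shift. Residual variance per administration is s²/2, and a shift adds δ²/2 to the denominator of the absolute-agreement ICC. With δ = 0.105s, the added term is 0.105² = 0.011 of the residual variance. Using two of the protocol's own cut-offs as illustrations:

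- ICC 0.75 without drift becomes 0.75/(0.75 + 0.25 × 1.011) = 0.748.
- ICC 0.90 without drift becomes 0.90/(0.90 + 0.10 × 1.011) = 0.899.

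The ICC would barely register it.

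**What the retest patients can contribute.** In units of the SD of change, equal SDs assumed, 364 transplanted and 60 retest patients:

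- 95% half-width for the difference in mean change: 1.96 × √(1/364 + 1/60) = 0.27.
- 95% half-width for the retest change alone: 1.96/√60 = 0.25.
- Difference detectable with 80% power: (1.96 + 0.842) × √(1/364 + 1/60) = 0.39 (0.40 with 291 transplanted patients).

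| True difference (SD) | Power |
|---|---|
| 0.2 | 30% |
| 0.3 | 58% |
| 0.4 | 82% |
| 0.5 | 95% |

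**Illustration.** Suppose the observed SRM is 0.5. The documents give no drift figure, so take 0, 0.1 and 0.2 SD in the same direction as assumptions. The change beyond retest is then 0.5, 0.4 and 0.3 SD. In the last case the 95% interval is 0.30 ± 0.27, or 0.03 to 0.57.

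**The case against.** The strongest reply is that the protocol claims little. Its definition is broad, and a paired test with an SRM is an accepted minimum for it. The phrase about exposure can be read as marking a time window rather than a cause. Sensitivity to change is not among the third-phase aims listed under Objectives, and no decision depends on it. Most of this stands, and it is why the point is a minor one. It does not remove the need to say what a significant result would mean, because a response to a changed state still has to be told apart from a response to being asked again.

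A second reply is that drift is handled by the absolute-agreement ICC, which falls when scores shift systematically. That is true in principle, but at the sizes that matter here the fall is about 0.001 to 0.002.

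A third reply is that the retest group is a poor reference. It is small and not randomised, and it comes from an earlier phase that uses the pilot questionnaire. It consists of waiting-list patients rather than patients just scheduled for surgery. It is retested after six weeks (Pilot questionnaire administration) or one month (Abstract), two statements that need reconciling, against more than three months here. This stands in full. It rules out a strict rule that denies sensitivity unless the retest change is exceeded, since power is only 58% at a difference of 0.3 SD. It does not rule out reporting the retest change alongside.

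**Conclusion.** The point holds as a limit on interpretation. As planned, a significant signed rank result is compatible with an SRM as low as about 0.11 (364 pairs, roughly normal differences). Alone, it cannot distinguish response to a changed state from re-administration drift, and it cannot attribute a shift to immunosuppressants rather than to transplantation as a whole.

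A reader might infer more than the documents support:

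- That any shift would count as responsiveness. It would not: the SRM cut-offs grade magnitude, and 0.11 is neither moderate nor large. What they do not address is the source of the shift.
- That a month 3 shift undermines the predictive validity analysis. It does not: the AUROC depends on how baseline scores rank patients who later are or are not non-adherent, and a later movement of the mean leaves that ranking unchanged.
- That the items refer to different medicines after surgery, or that teaching between visits moves the score. No KATITA item is shown and no such teaching is described.
- That the retest patients would isolate the drug effect. They bound re-administration drift to about ±0.25 SD and no more.

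This is an inexpensive improvement, not a flaw in a main objective.

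**What to change.** In the External validity assessment section:

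1. Keep the signed rank test and the SRM as planned.
2. Add the mean change and SD of change, scored on the final KATITA items, in the waiting-list test-retest patients, excluding anyone transplanted before retest.
3. Add the difference in mean change, transplanted minus retest, with its 95% confidence interval.
4. Base the interpretation on the size of the SRM read against the retest change, not on p<0.05 alone.
5. Describe the result as change from before to after transplantation, not as an effect of immunosuppressant exposure.

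The cost is one extra analysis and some wording; both data sets are already planned. The downside is the weakness of the reference: small, non-randomised, from an earlier phase and with a shorter interval. It bounds re-administration drift only and cannot resolve small differences. These limits should be stated with the result.
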